### Outcomes and measurements

2.6

A research assistant who does not know the randomization scheme will perform the data collection and examinations at baseline (T0) and in the week immediately post-intervention (T1). Every time to measure data is face-to-face with participants. We expect the intervention to improve the abilities of patients to take care of themselves. Therefore, we choose the activities of daily living measured in the week immediately post-intervention (T1) as the primary outcome. Self-esteem, rehabilitation self-efficacy, positive emotion, upper limb function, and safety will be the secondary outcomes.

#### Demographic data (T0)

2.6.1

To characterize the participants, the sex, age, educational level, marital status, residence, nationality, religion, monthly income *per capita* of family, type of medical insurance, diagnosis, phase of stroke, type of combined chronic disease, Brunnstrom stage, and main caregivers will be collected.

#### Self-esteem

2.6.2

Self-esteem will be evaluated by the self-esteem scale with a single dimension and 10 items, which was compiled by Rosenberg in 1965 (29). Each item on the Chinese version of the self-efficacy scale is scored from 1 (quite wrong) to 4 (quite right). The total score ranges from 10 to 40 and a higher total score indicates a higher sense of self-efficacy. The Cronbach’s alpha of this scale is 0.83 (30), meaning good reliability.

#### Rehabilitation self-efficacy

2.6.3

Rehabilitation self-efficacy will be measured by the Stroke Self-Efficacy Questionnaire compiled by Jones et al. in 2008, which is used to evaluate the functional performance and confidence of self-management of patients with stroke in the recovery period (31). Li et al. translated and revised it into Chinese with two dimensions, including activity of daily living efficiency and self-management efficiency (32). This scale has 11 items and each item is scored from 1 (very unconfident) to 10 (very confident). The total score ranges from 11 to 110, and a higher total score indicates a higher sense of rehabilitation self-efficacy. The Cronbach’s alpha of this scale is 0.969 (32).

#### Positive emotion

2.6.4

The positive emotion dimension of the Positive Affect and Negative Affect Scale will be used to measure positive emotion in patients with stroke. This scale was developed by Watson et al. in 1988 and revised by Qiu et al. in 2008 (33). The positive emotion dimension has nine items and each item is scored from 1 (never) to 5 (almost). The total score ranges from 9 to 45, and a higher total score indicates more positive emotions. The Cronbach’s alpha of this scale is 0.92 (34).

#### Upper limb function

2.6.5

Upper limb function will be measured by the Fugl-Meyer Assessment, which is one of the important scales for evaluating the motor function of stroke patients, with the advantages of reliability and high sensitivity (35). The upper limb dimension of the simplified Fugl-Meyer Assessment has 33 items. Each item is scored from 0 (cannot be completed) to 2 (completed). The total score ranges from 0 to 66. The higher the total score, the better the motor function of the upper limbs and hands.

#### Activities of daily living

2.6.6

The modified Barthel Index will be used to evaluate the activities of daily living. This scale has 10 items, and each item is divided into 5 levels according to the degree of dependence (36). The total score ranges from 0 to 100. The higher the total score, the better the self-care ability.

#### Safety outcomes and adverse events

2.6.7

All adverse events, such as pain, joint dislocation, and fracture, will be continuously measured during the rehabilitation period. Information about the severity, duration, and correlation to intervention of adverse events will be recorded in detail.

### Statistical analysis plan

2.7

#### Statistical methods

2.7.1

We will use IBM SPSS Statistics 22 to analyze the data, and all tests are two-sided. Statistical significance is defined as a *p*-value of <0.05. Confidence intervals (CIs) will be stated at the 95 confidence level. A P–P diagram will be used to test the normal distribution of measurement data. The statistical description of measurement data will use the mean and standard deviation when following a normal distribution; otherwise, use the median and quartile. When following normal distribution and homogeneity of variance, the measurement data will be compared by the analysis of variance for intergroup comparison, a paired-sample t-test will be used for intragroup comparison, and a multifactorial analysis of variance will be used to evaluate the interaction effects. Otherwise, the Kruskal–Wallis H-test will be adopted for intergroup comparison, and the Wilcoxon signed rank sum test will be used for intragroup comparison. Counting data will be described by number and percentage. The chi-square test and Fisher’s exact test will be used to analyze the counting data. If the baseline indicators are not comparable, an adjustment to the efficacy contrast of variables such as age, sex, and diagnosis is required. In patients where baseline indicators are unbalanced, an adjustment to the efficacy contrast of variables such as age, sex, and concurrent therapy is required. The covariance approach will be used for continuous variables, and logistic regression analysis will be used for counting data.

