### Study setting

2.1

This trial will be conducted at the West China Hospital of Sichuan University in Chengdu, China. Stroke patients aged 60 years and older with upper limb dysfunction who are hospitalized in the Department of Neurology of this hospital will be recruited. The department is a national key clinical specialized department, which ensures that enough participants can be recruited for this trial. It is estimated that 10 stroke patients aged 60 and above can be accommodated per month, who are expected to be hospitalized for up to 20 days and can accept rehabilitation training for 3 weeks. Therefore, in accordance with the availability of the patients and a loss of follow-up rate of 10 to 15%, we plan to recruit 12 stroke patients aged 60 and above first to conduct a pilot study. The sample size will be calculated using PASS software based on the scores of activities of daily living after the pilot study. Each group will have no less than 35 people.

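### The baseline Barthel score is not prespecified as a covariate for the primary comparison; adjustment is triggered only by observed imbalance

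*Protocol article*

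**What the plan says.** Section 2.6 of the protocol article fixes the endpoint: "we choose the activities of daily living measured in the week immediately post-intervention (T1) as the primary outcome". The opening of section 2 says that every outcome is collected at T0 as well as T1, so each randomised patient should have a baseline modified Barthel score (0 to 100, section 2.6.6).

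Section 2.7.1 gives the between-group test. When normality and equal variance hold, "the measurement data will be compared by the analysis of variance for intergroup comparison". "Otherwise, the Kruskal–Wallis H-test will be adopted for intergroup comparison". No covariate is attached to either test.

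The same section adds two further elements:

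- A multifactorial ANOVA is planned for interaction effects. Its factors are not named.
- Covariance adjustment is required when baseline indicators are not comparable or are unbalanced. The examples are age, sex and diagnosis in one sentence, and age, sex and concurrent therapy in the next. Both lists are open-ended, and neither names the baseline Barthel score.

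On size, section 2.1 says: "Each group will have no less than 35 people". It also says: "The sample size will be calculated using PASS software based on the scores of activities of daily living after the pilot study".

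**The concern.** In a randomised trial with a continuous outcome measured before and after treatment, the baseline value of that outcome is usually the strongest available predictor of the final value. Putting it in the model removes the variance that it explains. That gain depends on the correlation between T0 and T1, not on whether the arms happen to differ at baseline. A rule that adjusts only after imbalance is seen therefore forgoes the gain in just those trials where the arms look alike.

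The rule also leaves the form of the primary analysis to be settled from the trial data. The article gives no threshold for imbalance, and it does not say which result is primary if adjusted and unadjusted results differ. The Kruskal–Wallis branch cannot take in the baseline score and yields no mean difference with the 95% CI that section 2.7.1 promises.

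At stake is precision on the primary endpoint in a trial whose stated minimum is modest. The unadjusted comparison remains valid under randomisation; it is less efficient than it need be.

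**Working it through.** **The plan's own figure.** The 35 per arm cannot be reproduced, because no effect size, SD, power or T0–T1 correlation is given. Inverting the usual normal-approximation formula shows what it corresponds to for two arms at 80% power: (1.960 + 0.842) × √(2/35) = 0.67 SD.

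**Inputs from the article.**
- Section 2.7.1: "all tests are two-sided", and "Statistical significance is defined as a *p*-value of <0.05".
- Section 2.1: 35 per arm, as a minimum.

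**Inputs assumed.**
- True pairwise difference of 0.5 SD of the T1 score.
- T0–T1 correlation r from 0.3 to 0.8.
- Equal SDs at T0 and T1, needed only for the change-score column below.

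**Method.** Pairwise power comes from the noncentral t distribution with 68 degrees of freedom (critical value 1.995) and noncentrality (0.5/s) × √(35/2). Here s is the error SD in units of the T1 SD:
- T1 score alone: s = 1.
- ANCOVA on the T0 score: s = √(1 − r²).
- Change from baseline: s = √(2(1 − r)).

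The one degree of freedom spent on the covariate changes power by less than 0.1 percentage point.

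*Unadjusted:* noncentrality 0.5 × √17.5 = 2.09, power 54%.

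*Worked ANCOVA case, r = 0.7:* s = √(1 − 0.49) = 0.714; 0.5/0.714 = 0.70; noncentrality 0.70 × √17.5 = 2.93; power 82%.

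| r (assumed) | T1 alone | Change score | ANCOVA | ANCOVA gain over T1 alone (points) | Difference detectable at 80% power, ANCOVA |
|---|---|---|---|---|---|
| 0.3 | 54% | 41% | 58% | 4 | 0.65 SD |
| 0.5 | 54% | 54% | 66% | 12 | 0.59 SD |
| 0.6 | 54% | 64% | 73% | 19 | 0.54 SD |
| 0.7 | 54% | 76% | 82% | 28 | 0.49 SD |
| 0.8 | 54% | 90% | 93% | 39 | 0.41 SD |

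Without adjustment, the difference detectable at 80% power is 0.68 SD on the same basis.

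**Three-arm test.** The planned ANOVA is an omnibus F test, so the pairwise figures are not its power. With equally spaced means (0, 0.25 and 0.5 SD), the noncentrality is 35 × 0.125 = 4.375 on 2 and 102 degrees of freedom, and power is 44%. With the T0 score as covariate, the noncentrality is divided by 1 − r². Power becomes 48%, 56%, 63%, 74% and 88% for the same five values of r. The pattern is the same.

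**Change score against ANCOVA.** Because 2(1 − r) exceeds 1 − r² by (1 − r)², the change score has the larger error variance at every r below 1. At r = 0.3 it is worse than ignoring baseline; at r = 0.5 it equals ignoring baseline.

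**The case against.** Four points can fairly be made for the plan.

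1. *Section 2.7.1 does plan covariance adjustment, with an open list.* A visible gap in baseline Barthel score would fit the term baseline indicators, and the list does not exclude it. This stands. A reader might infer that the plan shuts the baseline score out or leaves every chance gap uncorrected, and the text does not support that. What remains is that the score is not named and that its use depends on observed imbalance.

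2. *The interaction ANOVA may use T0.* With two time points, group by time is a plausible reading, so it would be too flat to say that the plan tests T1 alone. On that reading the shortfall against ANCOVA shrinks to about 6 points at r = 0.7 and 3 at r = 0.8. But the factors are unnamed, the analysis is listed apart from the between-group comparison, and a change-score test does no better than T1 alone at r = 0.5 and worse at r = 0.3.

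3. *The correlation is unknown.* This also stands. Entry across Brunnstrom I to VI and from acute to chronic stroke, with about three weeks between measurements, makes a substantial r plausible. Yet acute patients recovering at different rates could lower it. A claim that much of the power is wasted is therefore conditional.

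4. *35 per arm is a minimum.* Correct: the final number is to follow from pilot data, so the percentages above do not describe the final design. The relative inefficiency remains at any sample size.

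**Conclusion.** The point holds in a limited form. The primary comparison does not commit to using the baseline Barthel score, although that score is collected. Adjustment waits on observed imbalance, and the one listed analysis that might use T0 is undefined.

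The direction is secure: ANCOVA gains at every r in the range shown. The size is not secure. For a pairwise contrast at 35 per arm and an assumed 0.5 SD difference, the gain over an unadjusted comparison runs from about 4 points at r = 0.3 to 12 at 0.5, 28 at 0.7 and 39 at 0.8. It is small at the low end and substantial from about 0.5.

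A reader might infer that the trial is underpowered or its primary estimate biased. The article supports neither: the sample size is still to be set, and randomisation protects the unadjusted comparison from systematic bias. This is an improvement that costs almost nothing and should be made. It is not a fatal flaw.

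**What to change.** In section 2.7.1, state one primary analysis: ANCOVA of the T1 modified Barthel Index on group and T0 modified Barthel Index, reporting adjusted mean differences between arms with 95% CIs. Say that it is run whatever the balance check or the P–P plot shows. Use the same model for each secondary scale with its own T0 score. Keep Kruskal–Wallis as a sensitivity analysis, and name the factors and role of the multifactorial ANOVA or drop it.

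It is best to settle this before the sample size is calculated, so that the calculation matches the analysis. The cost is one degree of freedom per model and a wording change; no new data or patients are needed.

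### Section 2.7.1 lets a P–P plot and a variance check choose the primary test, so whether the trial compares mean Barthel scores or rank orderings is settled only after the data are seen

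*Protocol article*

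**What the plan says.** Outcomes and measurements (2.6) fixes the primary outcome: "we choose the activities of daily living measured in the week immediately post-intervention (T1) as the primary outcome". Section 2.6.6 names the instrument, "The modified Barthel Index will be used to evaluate the activities of daily living", and its scale: "The total score ranges from 0 to 100. The higher the total score, the better the self-care ability".

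Statistical methods (2.7.1) gives one rule for all continuous data and no separate rule for the primary outcome:

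- Normality check: "A P–P diagram will be used to test the normal distribution of measurement data". No criterion for reading the plot is given.
- If both conditions hold: "When following normal distribution and homogeneity of variance, the measurement data will be compared by the analysis of variance for intergroup comparison".
- If either fails: "Otherwise, the Kruskal–Wallis H-test will be adopted for intergroup comparison".
- The descriptive summary switches as well, from mean and SD to median and quartiles.
- In general terms: "Confidence intervals (CIs) will be stated at the 95 confidence level".

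The hypothesis at the end of the Introduction is that the combined treatment does better on activities of daily living. It names neither a mean nor any other summary measure.

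**The concern.** Two things are fixed badly.

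First, the quantity tested depends on the observed data. One branch compares means. The other asks whether scores in one arm tend to rank above those in another. On a bounded score these can disagree, and a plot without a reading rule decides which one becomes the primary result.

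Second, the variance condition points the wrong way. Kruskal–Wallis can be read as a test of location when the arms share shape and spread. Section 2.7.1 sends data to it precisely when spread has been found to differ. The usual response to unequal variances, if means are of interest, is Welch's test.

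At stake is what a significant or non-significant primary result means. On the rank branch, p<0.05 may reflect a difference in spread and shape with no difference in mean, and a real mean gain may be missed if the improved arm also becomes less variable.

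**Working it through.** **The plan's own figures.** The document states no rejection rate, Barthel mean, SD or power, so there is nothing to reproduce. The group size is only a floor (2.1), with the final number to follow a pilot of 12 patients.

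**Inputs from the document.** Three arms, 1:1:1 (2.3); at least 35 per arm (2.1); score 0–100 (2.6.6); two-sided 0.05 (2.7.1). Loss to follow-up of up to 15% (2.1) leaves 35 × 0.85 = 29.75, about 30 per arm.

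**Inputs assumed.** All means, SDs and shapes. Scores are 100 × Beta(mκ, (1−m)κ), rounded, with m = mean/100, s = SD/100 and κ = m(1−m)/s² − 1. Example: mean 75, SD 25 gives κ = 0.1875/0.0625 − 1 = 2, hence Beta(1.5, 0.5), skewness −1.0. Mean 75, SD 12 gives κ = 0.1875/0.0144 − 1 = 12.02, hence Beta(9.02, 3.01), skewness −0.6. The means are equal but the shapes are not, so the rank orderings differ.

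**Tests.**
- Kruskal–Wallis: H = 12/(N(N+1)) × Σ nⱼ(R̄ⱼ − (N+1)/2)², with N = 105, referred to χ² on 2 df. It responds to differences in mean rank, not in mean score.
- Welch: wⱼ = nⱼ/sⱼ², W = Σwⱼ, m̃ = Σwⱼmⱼ/W, L = Σ(1−wⱼ/W)²/(nⱼ−1). For three arms, F = [Σwⱼ(mⱼ−m̃)²/2]/(1 + L/4), on 2 and 8/(3L) df.
- Stand-in for the plan's gate: Shapiro–Wilk per arm at 0.05/3, or Levene at 0.05. This is a proxy, because the plan's check is visual.

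Each row uses 4,000 simulated trials; the Monte Carlo SE is about 0.3 points at 5% and at most 0.8.

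**Equal means, 35 per arm: percentage of trials rejecting**

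| Assumed scores | Kruskal–Wallis | Welch |
|---|---|---|
| Identical distributions (three shapes, incl. skew and ceiling) | 4.6–5.0 | 4.7–5.1 |
| Symmetric, mean 50, SD 15/22/28 | 5.8 | 5.2 |
| Mean 65, SD 15/20/25 | 6.8 | 5.1 |
| Mean 60, SD 12/20/28 | 8.4 | 5.5 |
| Mean 75, SD 12/20/20 | 11.3 | 5.2 |
| Mean 75, SD 12/18/25 | 19.8 | 5.4 |
| Mean 80, SD 10/16/22 | 28.2 | 6.3 |

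At 30 per arm, Kruskal–Wallis ranged from 7.1% to 24.4% over the four lower rows.

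**Sensitivity to the assumed shape.** Ceiling-censored normal scores with unequal SDs gave Kruskal–Wallis 6.2% (mean 65), 15.4% (75), 20.8% (80) and 40.4% (85), with Welch at 5.5–6.0%. The most extreme beta cases gave 71.2% (mean 80, SD 10/20/30) and 80.8% (mean 85, SD 8/15/25), with Welch at 6.4% and 7.2%. The size is thus driven by skew and by how far the SDs differ.

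**Does the gate matter?** In the unequal-SD scenarios the proxy gate sent 89–100% of data sets to Kruskal–Wallis, so the two-stage rule rejected at almost the Kruskal–Wallis rate. With equal SDs of 20 at mean 75, ANOVA held 5.1%, yet the gate still switched 98% of data sets.

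**Power, one arm moving from 75 to 82.**
- Its SD falls from 20 to 12: Kruskal–Wallis 19%, ANOVA 37%, Welch 46%.
- Its SD stays at 20: Kruskal–Wallis 49%, ANOVA 30%.

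**The case against.** The strongest reply is that nothing here is a false positive in the ordinary sense. If treatment does nothing, randomised arms share one distribution, and then Kruskal–Wallis rejects in 4.6–5.0% and the two-stage rule in 4.6–5.2% of trials, even with skew or a ceiling. Rejecting when means are equal but distributions differ is an error only for a mean target, which the protocol never states. The Barthel total is a sum of graded items, so rank ordering is a defensible target. All of this stands. A reader might infer that the plan runs a type I error of up to 28%; the document does not support that. Non-normality on the P–P plot does no such harm by itself either: the arms must differ in spread or shape.

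The high figures also need means well up the scale. Eligibility (2.2) spans Brunnstrom stages I to VI and all phases of stroke, so nothing shows that scores will sit near the ceiling. This stands too, and is why the figures are only illustrations.

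Three further inferences should be resisted:

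- **That the rank branch has no confidence interval.** Section 2.7.1 promises 95% intervals in general, and rank-based location-shift intervals exist. That the article names no estimator for this branch is detail an unseen analysis plan may supply.
- **That covariance adjustment is impossible there.** The adjustment sentence is triggered by baseline imbalance and is not confined to the ANOVA branch.
- **That normality is checked on pooled scores and not on residuals.** The text does not say; a within-arm check would be close to a residual check.

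Finally, the rank test is not uniformly worse. In the constant-SD scenario it has the clear advantage, 49% against 30%.

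What the reply does not remove is the rule itself. It is stated affirmatively, it leaves the primary target open until the data are seen, and it answers unequal variance with a test whose location reading depends on equal spread.

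**Conclusion.** The point holds as one of target and interpretation. The primary comparison is either of means or of rank orderings, depending on an unquantified plot and a variance condition, and unequal variance alone is sent to the rank test.

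Under assumed scaled-beta scores with 35 per arm, equal means and unequal SDs, Kruskal–Wallis rejects in about 5% of trials for symmetric scores and 8–28% for skewed ones, against 5–6% for Welch. Other assumed shapes widen the Kruskal–Wallis range to 5.8–81%, so 8–28% is neither a bound nor a prediction for this trial. No inflation arises when all arms share one distribution.

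The change is worth making before outcome data are analysed. It ranks below an essential correction, because rank ordering is a legitimate target if chosen in advance and because power can favour either test.

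**What to change.** In 2.7.1, remove the normality and variance gate for the primary outcome. State that the modified Barthel Index at T1 will be compared between arms by one mean-based analysis, whatever the P–P diagram shows, with unequal-variance standard errors (Welch, or a linear model with robust errors). Report mean differences between arms with 95% CIs. Keep Kruskal–Wallis as a labelled sensitivity analysis.

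If the sponsor prefers to keep a two-branch rule, the minimum change is that unequal variance leads to Welch's test and not to Kruskal–Wallis.

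The cost is a few sentences, with no added patients or measurements. The statistical price is real if the effect is a pure shift in a strongly skewed score: about 30% power for the mean-based test (ANOVA in that run) against 48–49% for Kruskal–Wallis in the constant-SD scenario. The opposite holds when the improved arm's spread shrinks: 45–46% for Welch against 17–19%. The abstract describes the trial as under way, so the change should be dated and made before the outcome data are analysed by arm.

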## Discussion

3

This paper presents the study protocol of a randomized controlled trial, targeting older stroke patients with upper limb dysfunction. With this study, we will measure reminiscent music therapy combined with robot-assisted rehabilitation intervention and expect this intervention to promote the health status and self-care abilities of older patients with upper limb dysfunction after stroke. The novelty of reminiscent music therapy combined with robot-assisted rehabilitation lies in the combination of music therapy, reminiscence therapy, and robot-assisted rehabilitation. Given the fatigue and negative emotions that are easily generated by older stroke patients in the process of rehabilitation training, which affect their cooperation in rehabilitation treatment and hinder rehabilitation progress, we combine reminiscent music therapy with robot-assisted rehabilitation.

Neurological rehabilitation is of great significance for the prognosis of strokes. Upper limb dysfunction, especially in the hand, leads to more disabilities because its functions are more complex and vital to daily life (37). To deal with this problem, many approaches, including robot-assisted rehabilitation, have been suggested for upper limb and hand rehabilitation following stroke (38). The robot-assisted upper limb training is purposed to improve hand function and motor, sensory, and cognitive function by combining visual feedback with motivation (38). The clinical utility of robot-assisted rehabilitation has been increasing (39). Adding robot-assisted rehabilitation to usual rehabilitation could provide greater changes in the upper limb rehabilitation of stroke patients compared to usual rehabilitation alone (37). Reminiscence therapy has become one of the most feasible and effective social psychological interventions and can guide older people to review and re-experience past lives, which generates a new interpretation of life and helps older people to understand themselves, reduce the sense of loss, and increase self-esteem (40). Recalling happy events helps individuals maintain a positive self-image and improve self-esteem and happiness. On the contrary, recalling sad events helps individuals examine past situations so as to increase their ability to adapt to the existing environment and achieve self-integration (41, 42). Music is one of the most common triggers of nostalgia, and touching off memories with familiar songs could significantly improve the mental health of older people (24). Importantly, some studies suggest that the combination of music and rehabilitation will significantly improve the effect of rehabilitation training (26, 43).

Therefore, this study intends to combine reminiscent music therapy with robot-assisted rehabilitation in order to enable older stroke patients to carry out upper limb rehabilitation training under the stimulation of reminiscent music. To the authors’ knowledge, this is the first study to examine the effects of reminiscent music therapy combined with robot-assisted rehabilitation in older stroke patients with upper limb dysfunction. In our opinion, using reminiscent music to stimulate nostalgia may help stroke patients obtain a sense of perfection and satisfaction from memory and help them to maintain self-concept and enhance their sense of self-worth, so as to improve self-esteem, decrease negative emotions, and accept the conditions. It is conducive to improving rehabilitation self-efficacy, changing into a positive attitude toward disease, and reducing post-stroke fatigue. If the patient participates in the treatment and rehabilitation of the disease with a positive attitude and action, it will help to promote the recovery of the disease and improve the prognosis.
